### Feasibility Trial

#### Objectives

The objectives of the feasibility trial are to (1) test the acceptability, feasibility, and implementation of the adapted BA intervention (BIP) and (2) test if a randomized controlled feasibility trial can be delivered effectively and estimate important parameters needed to design a future definitive trial.

This will be achieved by answering the following research questions (RQs): (1) what are the recruitment and retention rates for participants in the trial? (2) What is the feasibility and acceptability of the proposed randomization and data collection procedures? (3) To what degree can the BIP be implemented as planned? (4) What is the acceptability of the BIP from the perspective of study participants and BA counselors?

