### Intervention Arm

Participants in the intervention arm will receive the BIP, delivered by trained nonmental health specialists (BA counselors) who will be specifically recruited for the study. BA counselors will be supervised by a mental health specialist.

The BIP will be delivered over 6 sessions lasting 30-40 minutes over a period of 6-12 weeks, with a minimum of one week between sessions. All sessions will be delivered remotely, by telephone. An alternate telephone number will be collected at the time of recruitment to ensure the unhindered delivery of BA sessions to the client.

The components of BIP include structured sessions where participants, with the BA counselors, plan and identify 3 types of activities. The first one includes routine and necessary activities that are done either regularly or on a daily basis, for example, getting fresh, taking a bath, cooking, doing household chores, etc. Second, social activities involve interacting with other people, for example, meeting or chatting with people from the neighborhood, etc. And third, pleasurable activities include activities that one enjoys and has fun with. For example, reading a newspaper or book, watching television (serials and movies), etc. The BA counselor and the participant will both have a flipbook for guidance and a better understanding of the activities during the session, as it contains a pictorial representation of each type of activity. The BA counselor will follow a manual and maintain the session logs of the participants. The BA counselor in the session log will not only maintain the session details but also keep a record of the daily activities done by the participants and the mood associated with doing these activities through telephonic follow-up in between the sessions. Another reason this is done is to check if the participants are doing the activities or if they are facing any challenges while doing them.

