### Control Arm

Participants in the control arm will receive an EUC leaflet describing depression and its treatment and signposting, including providing contact details (addresses and telephone numbers) to help access usual care for depression. They will also be provided with 1-time brief advice on the same from the research assistants (RAs) remotely.

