### Trial Sample Size

The sample size is set to enable reliable estimation of recruitment and retention rates and to adequately explore the feasibility of data collection and intervention delivery in this feasibility trial. A total of 56 participants will be recruited for this study. This should be adequate to estimate a participation rate of 20% and a follow-up rate of 80% to within a 95% CI (with SD of 5% and 10%, respectively).

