### Quantitative Data Analysis

Analyses will be conducted using Stata software. The number of participants who were screened, randomized, treated, and followed up for the primary outcome (PHQ-9) [23] will be reported in a CONSORT (Consolidated Standards of Reporting Trials)-style flowchart [28]. The number of study completers, by trial arm, will be calculated as a proportion of the number randomized at baseline.

The proportion of baseline and outcome measures completed out of those planned and presented by the treatment allocation arm will also be calculated. The normality of the data will be assessed, and based on that, an independent *t* test or Mann-Whitney *U* test will be used to compare the intervention and the EUC arm.

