### Qualitative Data Collection: Interviews (Implementation, Mechanisms of Impact, and Context)

A subsample of 16 participants will be interviewed. We will purposively sample to ensure a mix of participants (intervention and control arms, men and women, aged 60 years or younger and aged 60 years or older, and completed or dropped out of BIP). The interviews will seek in-depth feedback on the topics explored in the brief survey as well as explore individual and context barriers and drivers to performing the 3 types of activities (routine and necessary, social, and pleasurable).

Once delivery of the BIP is completed, a group interview will be conducted with the 4 BA counselors to explore their experiences, including the acceptability of the interventions and the barriers and drivers to delivery, including contextual factors such as remote delivery.

All interviews will be conducted in the local language, face-to-face using topic guides, and digitally audio-recorded. A hermeneutics approach, which encourages participants to discuss features of the intervention to elicit data on their experience and evaluation of its delivery or receipt, will be used with trial participants, family members, and health care staff [31].

Trial participants will provide written informed consent for these interviews within their trial consent.

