### Ethical Considerations

Ethics and other relevant approvals on the protocol have been secured from the University of York Health Sciences Research Governance Committee (HSRGC/2020/418/B; November 27, 2020); the Health Ministry Screening Committee, India (2020-9330; June 12, 2020); and the ethics committee, NIMHANS’s Behavioral Sciences Division (NIMHANS/EC [BEH. SC.DIV.] 22nd MEETING/2OI9; February 3, 2020). The trial is also registered under the Clinical Trial Registry of India (CTRI/2020/05/025048; May 6, 2020).

Approvals for necessary amendments adjusting to the COVID-19 pandemic situation have been provided by the institutional ethics committee, Behavioral Sciences Division, NIMHANS.

The following amendments are made to the protocol:

In the first amendment to the protocol dated September 25, 2020, the focus group discussions and interviews as part of the survey of organizational capacity were shifted from face-to-face to telephonic mode.In the second amendment to the protocol dated May 15, 2021, the recruitment process was shifted from face-to-face to telephonic mode, and NCD counselors were involved in preliminary screening. A total of 4 BA counselors of the same cadre as the NCD counselors were recruited into the study to deliver the BA sessions.In the third amendment to the protocol dated January 27, 2022, process evaluation interviews are to be conducted at 8 weeks instead of 12 weeks, that is, immediately after the participants in the intervention group complete their 6 BA sessions and in the control group at 8 weeks after the participants receive their brief advice from the RAs postbaseline assessment.

Participants in the intervention group will receive INR 250 (US $3.01) per session, and participants in the EUC group will receive INR 250 (US $3.01) for attending the one-time brief advice.

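### The planned between-arm test ignores possible clustering by the four counselors who deliver BIP, so the uncertainty of that comparison is understated if counselors differ

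*Protocol article*

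**What the plan says.** Under Quantitative Data Analysis the protocol article calls PHQ-9 the primary outcome. It says that, depending on a normality check, an independent t or Mann-Whitney U "test will be used to compare the intervention and the EUC arm". Counselor is not mentioned there.

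The delivery of treatment is described elsewhere:

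- Intervention Arm: BIP is "delivered by trained nonmental health specialists (BA counselors) who will be specifically recruited for the study".
- Ethical Considerations, second amendment: "A total of 4 BA counselors of the same cadre as the NCD counselors were recruited into the study to deliver the BA sessions". The section on qualitative interviews repeats the number: "a group interview will be conducted with the 4 BA counselors".
- Control Arm: participants receive a leaflet and "1-time brief advice on the same from the research assistants (RAs) remotely". They have no counselor.
- Trial Sample Size: "A total of 56 participants will be recruited for this study". Randomization is individual and 1:1, so about 28 participants receive BIP.

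The second objective of the feasibility trial is to test whether such a trial can be delivered and to "estimate important parameters needed to design a future definitive trial".

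**The concern.** BIP participants are treated through repeated one-to-one telephone sessions by one of a few counselors. If some counselors obtain better results than others, outcomes of participants who share a counselor are correlated. Because controls have no counselor, the data are then partially nested: clustered in one arm and independent in the other. A t test or Mann-Whitney U test on individual participants is exact in its error rate only if that correlation is zero.

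The stakes are moderate. The Discussion links progress to a full trial to BIP being feasible and potentially beneficial. If the arm comparison feeds that judgement, its uncertainty should not look smaller than it is. A description of how outcomes, session completion and retention vary by counselor would also help in designing the definitive trial.

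**Working it through.** **The plan's own figure.** The sample size rests on estimating a 20% participation rate to within 5% and an 80% follow-up rate to within 10%. With half-width = 1.96 × √(p(1−p)/n):

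- follow-up: 1.96 × √(0.80 × 0.20/56) = 10.5%;
- participation: 56/0.20 = 280 approached, and 1.96 × √(0.20 × 0.80/280) = 4.7%.

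Both agree with the stated figures to rounding. Neither uses the arm comparison, and no power, effect size, alpha or ICC is given for that comparison.

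**Inputs for the check.** From the document: 56 participants, 1:1 allocation, four counselors in the BIP arm only. Assumed, because the document is silent: 28/4 = 7 participants per counselor (even caseload), one counselor per participant for all sessions, equal total variance in the arms, and a range of ICC values.

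**Formulas.**

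- Design effect in the BIP arm: DE = 1 + (m − 1) × ICC, with m = 7.
- True SE of the arm difference divided by the naive SE: R = √((DE + 1)/2).
- Amount by which the naive SE is too small: 1 − 1/R.
- Actual two-sided error of a nominal 5% test: 2 × (1 − Φ(1.96/R)).

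Example at ICC 0.10: DE = 1 + 6 × 0.10 = 1.60; R = √(2.60/2) = 1.140; 1 − 1/1.140 = 12.3%; error 8.6%.

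| ICC | DE | R | Naive SE too small by | Error, formula | Error, simulated t test |
|---|---|---|---|---|---|
| 0 | 1.00 | 1.000 | 0% | 5.0% | 5.0% |
| 0.01 | 1.06 | 1.015 | 1.5% | 5.4% | 5.4% |
| 0.05 | 1.30 | 1.072 | 6.7% | 6.8% | 6.6% |
| 0.10 | 1.60 | 1.140 | 12.3% | 8.6% | 8.5% |
| 0.20 | 2.20 | 1.265 | 20.9% | 12.1% | 12.3% |

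The simulation used 40,000 runs per ICC, with four counselors of seven participants against 28 controls.

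**Mann-Whitney U.** In 4,000 runs per ICC the error was 5.6% at ICC 0, 6.6% at 0.05 and 7.8% at 0.10. The non-parametric option does not avoid the problem.

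**With 80% follow-up.** 28 × 0.80 = 22.4 per arm and 22.4/4 = 5.6 per counselor. By the same formulas the naive SE is 1.1%, 5.3% and 9.8% too small at ICC 0.01, 0.05 and 0.10, and the error is 5.3%, 6.3% and 7.7%.

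**Can the trial estimate the ICC?** At a true ICC of 0.05 with four counselors of seven, the central 95% of ANOVA estimates ran from −0.15 to 0.37, and 46% were zero or below. In such samples a fitted random effect would be at or near zero and correct little or nothing.

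**Does a workable alternative exist?** Taking counselor means as the unit in the BIP arm, with Satterthwaite degrees of freedom, gave a simulated error of 5.1% to 5.5% for ICC 0 to 0.20.

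**The case against.** The strongest reply is that the comparison carries little weight. The research questions and stated outcomes concern recruitment, retention, data completeness, acceptability and implementation, and no progression rule is tied to a p-value. This stands, and it keeps the point modest. It does not remove it, because the article itself names PHQ-9 as primary and fixes the test.

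Second, the document gives no ICC, no caseload, and no statement that each participant keeps one counselor. If counselors covered for each other, strict nesting would fail. This also stands, so the size can only be given conditionally.

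Third, this is a condensed article, and tables by counselor may be in a full protocol or analysis plan that is not shown. Counselors are also covered by the fidelity sample and the group interview. That is fair: the absence of such tables is no fault in itself. The choice of test, however, is stated here and not left open.

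A reader might infer more than the documents support:

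- *That the intervals are certainly too narrow.* This needs an ICC above zero; at 0.01 the effect is negligible. The article names a test and no interval for the arm difference.
- *That the naive SE is 14% too small at ICC 0.10.* The true SE is 14% larger than the naive one, which makes the naive SE 12.3% too small.
- *That 56 is the wrong sample size.* It was chosen for participation and follow-up rates, not for this comparison.
- *That the trial should deliver a counselor ICC for planning.* Four counselors cannot do so. Under Limitations the article adds that they were recruited for the study and lacked familiarity, so transfer to routine NCD counselors is uncertain.

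**Conclusion.** The point holds in conditional form. The named tests do not match a design in which four counselors deliver therapy in one arm only. If counselors differ, the arm comparison looks more certain than it is: by little at ICC 0.01, and enough at 0.05 to 0.10 to move a nominal 5% error to about 6.7% to 8.6%, or about 6.3% to 7.7% after 20% loss. These figures rest on assumed ICCs, an even caseload and one counselor per participant. The feasibility estimates that justify the sample size, and the recruitment rate, are untouched. This is a worthwhile, inexpensive improvement to a secondary use of the data and does not challenge the trial's main purpose.

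**What to change.** The Results section says that analysis is still under way, so the change can be made now.

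1. Keep the counselor identifier in the analysis data. Counselors maintain the session logs, so the link should be recoverable. State the actual caseloads and whether any participant changed counselor.
2. Report PHQ-9 change, sessions completed and retention by counselor, descriptively.
3. Present the arm difference as exploratory, with a confidence interval.
4. Add a sensitivity interval in which the BIP-arm variance is multiplied by 1 + (m − 1) × ICC at fixed ICCs of 0.05 and 0.10. Alternatively, analyse counselor means in the BIP arm with Satterthwaite degrees of freedom.
5. Do not rely on a fitted random effect, and do not offer an ICC from four counselors as a planning parameter. If it is shown, give it with its wide interval as description only.

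The cost is a few lines of wording and code, using data the trial should already hold. With seven per counselor, the sensitivity intervals would be about 7% and 14% wider at the two ICCs (R = 1.072 and 1.140).

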### Process Evaluation

The 3 key functions of a process evaluation (mechanisms of impact, context, and implementation) will underpin our approach for the feasibility trial [29]. The qualitative inquiry will be used in combination with quantitative data to gain a more complete picture.

### Survey (Implementation and Mechanisms of Impact)

To capture the views and experiences of participants, all participants will complete a brief quantitative survey at a 3-month follow-up. Participants in the intervention arm will be asked about their engagement with and acceptability of BIP, views on remote delivery, as well as the perceived impact on their depression symptoms. Control arm participants will answer these questions in relation to the EUC leaflet. Participants in both trial arms will also complete some questions to assess the acceptability of trial processes.

Potential mediators of intervention impact will be measured at baseline and 3 months: intentions, beliefs about capabilities, and beliefs about outcomes. These have been selected to reflect the hypothesized mechanisms of action of BA [30].

### Qualitative Data Collection: Interviews (Implementation, Mechanisms of Impact, and Context)

A subsample of 16 participants will be interviewed. We will purposively sample to ensure a mix of participants (intervention and control arms, men and women, aged 60 years or younger and aged 60 years or older, and completed or dropped out of BIP). The interviews will seek in-depth feedback on the topics explored in the brief survey as well as explore individual and context barriers and drivers to performing the 3 types of activities (routine and necessary, social, and pleasurable).

Once delivery of the BIP is completed, a group interview will be conducted with the 4 BA counselors to explore their experiences, including the acceptability of the interventions and the barriers and drivers to delivery, including contextual factors such as remote delivery.

All interviews will be conducted in the local language, face-to-face using topic guides, and digitally audio-recorded. A hermeneutics approach, which encourages participants to discuss features of the intervention to elicit data on their experience and evaluation of its delivery or receipt, will be used with trial participants, family members, and health care staff [31].

Trial participants will provide written informed consent for these interviews within their trial consent.

### Fidelity Index (Implementation)

Fidelity in delivering BIP will be assessed using a fidelity index. This index consists of 2 subindices, namely, the adherence index, which assesses adherence to delivering the content of the 6 BIP sessions, and the interaction index, which assesses the level of counselor-participant with which the intervention was delivered. Both indices are scored on a 3-point Likert scale (0=not implemented, 1=partially implemented, and 2=fully implemented).

All BIP sessions will be audio-recorded. We will then perform the fidelity checks by reviewing the audio recording of a subsample (n=18) of sessions. These sessions will be purposefully selected to include a mix of sessions 1-6, delivered by all BA counselors early and late in the feasibility trial.

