### Fidelity Data Analysis

The quantitative data from the fidelity index and questionnaire will be analyzed using descriptive statistics, including means and SD for continuous variables and absolute and relative frequencies for categorical variables.

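### Fidelity is averaged over 18 purposively chosen recordings although every session is recorded; a random draw within the same mix would cost nothing

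*Protocol article*

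**What the plan says.** The third research question under Objectives asks: "To what degree can the BIP be implemented as planned". The Outcomes section sends implementation outcomes to the process evaluation, where the Fidelity Index section supplies the scored measure of delivery. It has an adherence part and an interaction part, each rated from 0 (not implemented) to 2 (fully implemented).

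On the source material, that section says "All BIP sessions will be audio-recorded". On how many are rated: "We will then perform the fidelity checks by reviewing the audio recording of a subsample (n=18) of sessions". On how they are chosen: "These sessions will be purposefully selected to include a mix of sessions 1-6"; the sentence goes on to ask for every counselor and for both early and late delivery. No random step is mentioned.

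The Fidelity Data Analysis section says that the index data will be "analyzed using descriptive statistics, including means and SD for continuous variables", with frequencies for categorical variables.

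On records of delivery, the Intervention Arm section says: "The BA counselor will follow a manual and maintain the session logs of the participants".

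**The concern.** A mean and SD will be read as a statement about how BIP was delivered in the trial. That reading needs a sample whose link to all delivered sessions is known. The stated criteria (session number, counselor, early or late) fix the mix that is wanted, but not which recording is taken within it. Whoever makes that choice can move the mean in either direction, even without intending to, and the article gives no means of telling whether this happened.

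Purposive choice suits the interviews, where the aim is breadth of experience. It suits a numerical average less well when a complete list of recordings exists and a random draw within the same factors needs no extra rating.

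There is a related limit on what the index means. A session that never took place has no recording, so the index measures the quality of held sessions and nothing else. Its reader needs the number of held sessions next to it.

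**Working it through.** **Plan's own figure.** The article gives no derivation or precision target for 18, so there is nothing to reproduce.

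**Inputs.** 56 participants (Trial Sample Size); 1:1 simple randomization (Randomization); six sessions each (Intervention Arm); four counselors (Ethical Considerations); 18 recordings (Fidelity Index).

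**Sampling fraction.** The expected BIP arm is 56/2 = 28, so 28 × 6 = 168 sessions are planned and 18/168 = 10.7%. Under simple randomization the arm size has a 95% range of 21 to 35. This gives 18/126 = 14.3% and 18/210 = 8.6%.

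**How far the criteria fix the choice.** Session number × counselor × period gives 6 × 4 × 2 = 48 cells, and session number × counselor alone gives 24. Eighteen recordings cannot fill either grid. They can cover each factor singly, for example 18/6 = 3 per session number. Many different sets of 18 meet the stated mix, and the text does not say how one is picked.

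**Effect of an unweighted mean.** Assume three recordings per session number and a constant loss of participants from one session to the next.

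| Assumed loss per session | Sessions held of 168 | Fraction rated, session 1 | Fraction rated, session 6 |
|---|---|---|---|
| 0% | 168 (100%) | 10.7% | 10.7% |
| 5% | 148 (88%) | 10.7% | 13.8% |
| 10% | 131 (78%) | 10.7% | 18.1% |
| 20% | 103 (61%) | 10.7% | 32.7% |

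Late sessions, which come from people who stayed, are over-represented. At 10% loss the average session number is 3.5 in the sample. Among held sessions it is Σk·0.9^(k−1) / Σ0.9^(k−1) = 14.97/4.69 = 3.2. If scores change linearly with session number, the unweighted mean is off by about 0.3 times the change per session. That is modest, and weighting removes it. The effect of judgement in choosing recordings cannot be computed.

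**What a random draw would give.** Treat 18 of 168 as a simple random sample and ignore clustering. The 95% half-width is t(0.975, 17) × SD/√18 × √(150/167). With an assumed SD of 0.3, 0.5 or 0.8 on the 0–2 scale, it is 0.14, 0.24 or 0.38.

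**What the index does not show.** Suppose the mean on held sessions is 1.8 out of 2. It reads 1.8 whether 80% (134) or 60% (101) of the 168 planned sessions were held.

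**The case against.** The strongest defence is that the selection is orderly and the claim modest. The criteria are stated in advance, are structural and have nothing to do with session quality. Covering every counselor, session number and period is a sensible aim in a feasibility trial. The analysis is descriptive, with no interval, test, threshold or statement about all sessions, and a mean and SD of 18 ratings is a correct description of those 18. A random draw would still give an interval of roughly ±0.24 at an assumed SD of 0.5, probably wider once clustering within counselors and participants is counted. All of this stands. It makes the point an improvement and not the correction of an error.

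A reader might go further and infer that the question on implementation rests on these 18 recordings alone, so that the trial cannot see missed sessions. The article does not support that. Counselors keep session logs. The process evaluation collects drop-out data (Data Management). Interviews include people who dropped out of BIP. The three-month survey asks about engagement. The flowchart reports the number treated (Quantitative Data Analysis). Only the index is limited to held sessions, and measuring the quality of what was delivered is its proper job.

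It is also tempting to count the lack of a named sessions-out-of-six table as a defect. No section shown names one, but a journal article may leave such a table to the full protocol.

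**Conclusion.** The concern holds in a limited form. The 18 rated recordings, about 11% of some 168 planned sessions, are chosen by judgement from a complete set. Their mean and SD therefore carry no design-based inference to the delivered sessions.

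The fraction assumes a BIP arm near 28 and all planned sessions held. The weighting illustration assumes equal numbers per session number and a constant loss rate. Neither the direction nor the size of any selection effect can be established from the article.

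Two further inferences should be avoided. Multiplying the fidelity score by the share of sessions held would merge quality with dose; they are separate quantities and should be shown separately. Bounding inadequate delivery at about 15% when all 18 sessions are adequate (1 − 0.05^(1/18) = 0.153) needs independent sessions and an adequacy cutoff. The sessions are clustered within four counselors, and the protocol has no such cutoff.

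**What to change.** Keep 18 recordings and the stated mix, and change only how they are picked:

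- Fix the date that separates early from late. List all held sessions by counselor, period and session number.
- Draw by computer at random within the 4 × 2 = 8 counselor by early/late strata. That is two per stratum with two strata given a third (6 × 2 + 2 × 3 = 18), balanced to three per session number where recordings allow.
- Weight each rating by the inverse of its chance of selection, so that the mean refers to all held sessions.
- If rating is already done, leave the scores as they are and label the mean and SD as describing the selected sessions only.
- Beside the fidelity score, report from the session logs the number of sessions held out of six for every participant randomized to BIP, as a separate measure of dose.

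The cost is a random draw, a set of weights and one table. No further recordings need rating and no new data are collected. The article's Results section describes the analyses as ongoing, so the existing recordings and logs suffice.
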